**Methods:**

This prospective before-and-after self-controlled cohort study will evaluate the effectiveness of a 12-month internet-based intervention targeting university student MSM in Chengdu. A total of 484 HIV-negative student MSM among the MSM population will be recruited through WeChat and Blued. Trained student volunteers, supervised by community-based organization staff, will deliver monthly health education, one-on-one counseling, postexposure prophylaxis navigation, and HIV or sexually transmitted infection (STI) self-testing kits via secure online platforms. Participants will complete behavioral surveys and HIV/syphilis/hepatitis C virus/hepatitis B surface antigen self-tests at baseline, 6 months, and 12 months. Primary outcomes included changes in HIV and syphilis incidence rates; secondary outcomes included changes in sexual behaviors, HIV/STI testing frequency, preexposure prophylaxis/postexposure prophylaxis uptake, and knowledge improvement.

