### Survey Content and Follow-Up

Participants will complete a baseline questionnaire upon enrollment, which collects detailed information on sociodemographic characteristics, sexual behaviors, HIV-related knowledge, attitudes, practices, and other relevant behavioral factors (see Multimedia Appendix 3 for details).

Follow-up surveys will be administered at two time points post-intervention: 6 months and 12 months. The content of the follow-up questionnaires will be identical to that of the baseline survey to enable assessment of changes over time (see Multimedia Appendix 4 for follow-up questionnaire content). Data collection instruments and operational manuals have been standardized to ensure consistency in measurement and facilitate reproducibility across different investigators.

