#### PEP Assistance

For participants reporting high-risk exposures (eg, condomless anal intercourse or needle-sharing), volunteers will provide the following:

Rapid linkage to PEP services: Same-day appointment coordination with PEP-prescribing outpatient clinics using a geolocation database.

Financial assistance: A one-time subsidy of RMB 500 (US $70.88) will be provided upon verified PEP completion (submission of clinic-issued proof). All PEP referrals are monitored through CDC-verified reporting channels to ensure timely initiation and adherence support. Participants with repeated high-risk exposures were assessed for PrEP eligibility in accordance with the Expert Consensus on HIV PrEP in China [25].

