#### HIV Prevention Supply Distribution

Participants will receive a discreetly packaged prevention kit via third-party logistics, ensuring privacy protection. The kit will include condoms, water-based lubricants, and STI self-testing kits.

Participants will receive a discreetly packaged prevention kit via third-party logistics, ensuring privacy protection. The kit will include condoms, water-based lubricants, and STI self-testing kits.

Distribution will be limited to a one-time delivery per participant to optimize resource allocation.

Volunteers track delivery confirmation through the digital management platform.

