#### Secondary Outcomes

Secondary outcome measures include (1) changes in sexual behaviors (eg, condom use, number of sexual partners) before and after the intervention; (2) frequency of biomedical intervention utilization (eg, HIV testing, STI testing, PEP, PrEP use); and (3) changes in HIV and STI prevention knowledge and awareness levels.

Detailed definitions of outcome indicators, measurement methods, and data sources are summarized in Table 1.

**Table 1. T1:** Indicators of study outcomes.

Domain	Specific indicator	Definition	Data source
Primary outcomes			
HIV incidence	Comparison between intervention cohort and local student MSM attending university	New HIV cases confirmed by medical institutions per 100 person-years vs surveillance data (2025)	Laboratory reports at 12-month follow-up; CDC^b^ surveillance data
Syphilis incidence	Comparison between intervention cohort and local student MSM attending university	New syphilis cases confirmed by medical institutions per 100 person-years vs surveillance data (2025)	Laboratory reports at 12-month follow-up; CDC surveillance data
Secondary outcomes			
Behavioral Changes			
Risk behaviors	Condom use during anal intercourse Commercial sex engagement Multiple partners	% reporting “always use condoms” in past 3 months % reporting paid sex in past 3 months % with ≥2 sexual partners in past 3 months	Structured questionnaire
Substance use	Psychoactive substance use during sex	% reporting use of chemsex drugs in past 3 months	Structured questionnaire
Testing behaviors	HIV testing frequency STI^c^ screening	% tested for HIV in past 3 months % tested for STIs in past 3 months	Structured questionnaire
Biomedical uptake			
Prevention tools	Condom/lubricant use PrEP^d^/PEP^e^ utilization	% using condom/lubricant % PrEP/PEP initiations	Supply logs; pharmacy data
Attitudinal changes			
Prevention intention	Future condom use intent Testing willingness	% planning to use condoms % willing to undergo future HIV/STI tests	Structured questionnaire
Awareness changes			
Health literacy	PEP/PrEP knowledge HIV/STIs awareness	% correctly describing PEP/PrEP protocols % choosing the right core knowledge about HIV/STIs	Knowledge assessment

a MSM: men who have sex with men.

b CDC: Centers for Disease Control and Prevention.

c STI: sexually transmitted infection.

d PrEP: preexposure prophylaxis.

e PEP: postexposure prophylaxis.

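### Table 1 takes condom/lubricant use from supply logs, which record a single study delivery and so show neither use nor a baseline

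*Protocol article*

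**What the plan says.** The Secondary Outcomes section refers the reader to Table 1 for outcome definitions, measurement methods and data sources. Under Biomedical uptake, the Prevention tools row defines two percentages, printed together as "using condom/lubricant % PrEP/PEP initiations", and names "Supply logs; pharmacy data" as the source. The questionnaire is not listed in that row. It is the source for the risk-behaviour, substance-use, testing and intention rows; knowledge has its own assessment.

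On the supplies, the HIV Prevention Supply Distribution section says "Participants will receive a discreetly packaged prevention kit via third-party logistics, ensuring privacy protection", then "Distribution will be limited to a one-time delivery per participant to optimize resource allocation", and "Volunteers track delivery confirmation through the digital management platform". Table 2 ticks supply distribution at month 1 only.

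On the role of these outcomes, the abstract states that "secondary outcomes included changes in sexual behaviors, HIV/STI testing frequency, preexposure prophylaxis/postexposure prophylaxis uptake, and knowledge improvement". The Discussion treats PEP/PrEP uptake as an early marker of impact. The Survey Content and Follow-Up section says of the questionnaire: "The content of the follow-up questionnaires will be identical to that of the baseline survey to enable assessment of changes over time".

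**The concern.** The study has no control group. Each participant is their own control, so a behavioural indicator is informative only if it is measured in the same way before and after the intervention starts. A source that comes into being with the intervention cannot meet that condition.

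The supply log is such a source. It is also one step removed from the indicator: the definition speaks of using condoms or lubricant, while the record described is that a parcel arrived. If the row were reported as written, receipt of an intervention component would appear among the study's outcomes as uptake of prevention. The Discussion says incident infections will be rare and that the study will lean on proximal behavioural outcomes, so such a row could be read as evidence of effect.

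**Working it through.** The plan gives no numerical target for this indicator, so there is no figure of its own to reproduce. The check sets the sections side by side and then shows the size of the artefact.

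**Step 1: which source goes with which indicator.** The row has two indicators and two sources. Read in order, supply logs belong to condom/lubricant use and pharmacy data to PrEP/PEP initiations. No other pairing gives condom use a better source.

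**Step 2: what the supply log can hold.**

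| Property | What the protocol describes | What a before-after measure of use needs |
|---|---|---|
| Starts | Month 1 (Table 2) | Month 0 |
| Deliveries per participant | One | Not applicable |
| Repeat measurement | None after the delivery | Months 6 and 12 |
| Content recorded | Delivery confirmation | Use |
| Who is covered | All participants, by design | All participants |

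**Step 3: what the log would show.** Let *d* be the proportion of kits delivered, and *u*₀ and *u*₁₂ the true proportions using condoms or lubricant at months 0 and 12.

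- Log at month 0: 0, since nothing has been sent.
- Log at months 6 and 12: *d* at both, assuming delivery is complete by month 6.
- Apparent change, month 0 to 12: *d* − 0 = *d*.
- True change: *u*₁₂ − *u*₀, which appears nowhere in the log.
- Apparent change, month 6 to 12: *d* − *d* = 0, whatever participants do.

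The protocol gives no value for *d*. Taking 90% to 100% as an assumed range and the planned 484 participants:

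- *d* = 0.90: 0.90 × 484 = 435.6, about 436 participants; apparent rise 90 percentage points.
- *d* = 1.00: 484 participants; apparent rise 100 percentage points.

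Both figures hold when *u*₁₂ = *u*₀. A paired test would add nothing: with 436 discordant pairs all in one direction, the exact McNemar P value is 2 × 0.5^436, about 10^−131, with no change in behaviour. A lower *d* shrinks the artefact but does not turn it into a measure of use.

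**Step 4: what else in the plan covers the same ground.** The Risk behaviors row of Table 1 takes consistent condom use during anal intercourse over the past 3 months from the structured questionnaire, which is given at months 0, 6 and 12. That is a valid before-after measure of condom use. It does not cover lubricant, and it leaves the Prevention tools row as it is.

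**Step 5: PrEP/PEP.** The indicator is initiations. Table 1 names pharmacy data, but the article does not give their holder, period or any look-back before enrolment. The PEP Assistance section describes other records: "All PEP referrals are monitored through CDC-verified reporting channels to ensure timely initiation and adherence support", and clinic proof for the subsidy. These arise during the intervention, but Table 1 does not name them as the source. Nothing can be computed for this half.

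**The case against.** Four points can be made for the plan.

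- **Condom use already has a sound measure.** The questionnaire row described above supplies a baseline and both follow-ups. This stands and limits the harm. It does not correct a row whose definition is use and whose source is delivery.
- **The row may not be meant as a before-after outcome.** The Secondary Outcomes list speaks of changes for sexual behaviours and for knowledge, but of frequency for biomedical utilization, and no before-after test of supply-log data is spelled out. This stands in part. The abstract includes PrEP/PEP uptake among the changes, and the design is self-controlled, so the sections need to be aligned. Even as a simple frequency, a delivery log does not give the percentage using.
- **An article leaves source details to fuller documents.** That is fair for the coverage of the pharmacy data. It does not help with supply logs, where the article does name a source and the source does not fit.
- **Self-report has its own bias.** The Discussion acknowledges social desirability. This is a real cost of the fix.

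A reader might go further and infer that PrEP/PEP uptake also has a zero baseline by construction, that it records delivery and not use, and that courses obtained outside study referral are missed. The documents do not support this. They do not say that the pharmacy data begin with the intervention or belong to the study; dispensing records are a reasonable source for initiations; and the referral and subsidy records are not the source Table 1 names.

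**Conclusion.** The point holds for condom/lubricant use. Its named source cannot yield the indicator as defined, has no pre-intervention value, and would show a rise equal to the delivery rate whatever participants do. The 90 to 100 percentage points are an illustration that rests on an assumed delivery rate. The conclusion itself assumes only that the supply logs are the delivery-confirmation record, the only supply record the article describes.

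For PrEP/PEP the supportable point is narrower. The abstract and the Discussion treat uptake as a change and a marker of impact, while the article does not state whether the pharmacy data cover a comparable period before enrolment. That is a condition to be met before a before-after comparison is made; it does not show that the baseline is zero.

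The consequence is moderate. This is one secondary indicator, a valid questionnaire measure of condom use sits beside it, and the Discussion names HIV testing and PEP/PrEP uptake, not supplies, as its early markers. The row should still be corrected, because as written it would report receipt of the intervention as use.

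**What to change.** - **Condom/lubricant use:** in the Prevention tools row, name the structured questionnaire as the source, at baseline, 6 and 12 months, with the same recall period each time.
- **Supply logs:** keep them as an implementation measure (kits sent and received), without a before-after test.
- **PrEP/PEP initiations:** pharmacy data may remain the source. State the period they cover, and make a before-after comparison only if they cover a comparable pre-enrolment period for all participants. Otherwise take the change from the repeated questionnaire and report the records descriptively.
- **Wording:** make the abstract, the Secondary Outcomes list and the Discussion agree on whether biomedical uptake is a change or a frequency.

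The cost is mainly an edit to one row of Table 1, plus greater reliance on self-report; the records can be used to check follow-up answers on PrEP/PEP. The questionnaires are in appendices that are not shown. If they lack a lubricant or PrEP/PEP item, one must be added, and time matters: 127 participants had completed the baseline survey by the end of April 2025 (127/484 = 26% of the target). A baseline answer missing for them cannot be recovered later on the same footing.

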### Participant Timeline

Time schedule of enrollment, interventions, assessments, and visits for participants are presented in Table 2.

**Table 2. T2:** Schematic diagram for the schedule of enrollment, interventions, and assessments.

	Study period								
Timepoint and enrollment	Allocation	Postallocation							Close-out
	M0^a^	M1	M2	M3	M4	M5	M6	M7-11	M12
Enrollment									
Recruitment	✓								
Eligibility screen	✓								
Informed consent	✓								
Intervention									
Health education		✓	✓	✓	✓	✓	✓	✓	
Counseling services		✓	✓	✓	✓	✓	✓	✓	
HIV prevention supply distribution		✓							
PEP^b^ assistance		✓	✓	✓	✓	✓	✓	✓	
Assessments									
Baseline survey	✓								
Follow-up survey							✓		✓
Testing							✓		✓

a M: Month

b PEP: postexposure prophylaxis.

### Data Management

Survey data will be collected through Wenjuanxing, an online survey platform developed and operated by Ranxing Information Technology Co., Ltd., based in Changsha, China [26]. Wenjuanxing provides an automated data archiving system designed to ensure the integrity, security, and consistency of submitted responses.

All survey data will be stored on secure servers hosted by Alibaba Cloud in Hangzhou, China. The server infrastructure is protected by enterprise-level firewall systems, with daily automated data backups to prevent potential data loss and ensure disaster recovery capabilities.

Access to the database is strictly controlled through a role-based access control system. Only authorized research personnel, who have signed confidentiality agreements, will be granted access to view or manage the data. User authentication protocols, including secure passwords and encrypted data transmission, are implemented to further enhance data security and prevent unauthorized access.

### Statistical Analysis

Upon completion of data collection, all survey data will be exported from the Wenjuanxing platform for data cleaning and preprocessing to ensure accuracy, completeness, and consistency. Data management and analysis will be conducted using established statistical software packages, including SPSS, Stata, or R.

Descriptive statistics will be used to summarize participant characteristics and key study variables. Categorical variables will be presented as frequencies and percentages, while continuous variables will be reported as means with SD or medians with IQR, depending on data distribution. The normality of continuous variables will be assessed using Shapiro-Wilk tests and visual inspection of histograms/Q–Q plots. Univariate analyses, such as chi-square tests for categorical variables and *t* tests or nonparametric tests for continuous variables, will be used to assess preliminary associations between independent variables and outcome measures. Multivariate analysis will be performed using logistic regression models (for binary outcomes) to identify factors independently associated with key study end points, adjusting for potential confounders. If advanced statistical modeling (eg, Cox proportional hazards models, generalized estimating equations) is deemed necessary to address specific research questions or to handle longitudinal data, additional statistical expertise will be sought to ensure appropriate application and interpretation of these methods. A 2-sided *P* value <.05 will be considered statistically significant.

### Feasibility and Acceptability Evaluation

Feasibility will be assessed by examining recruitment and retention rates, completeness of follow-up surveys, and timeliness of testing. Acceptability will be evaluated through participant satisfaction surveys and qualitative feedback collected from peer volunteers regarding the practicality and perceived usefulness of the intervention materials. Descriptive statistics will be used to summarize feasibility and acceptability outcomes, and qualitative comments will be thematically analyzed.

## Results

Participant enrollment and data collection are currently ongoing. This trial protocol has been developed in accordance with the SPIRIT (Standard Protocol Items: Recommendations for Interventional Trials) 2013 guidelines [27].

As of May 1, 2025, the intervention materials and training program have been finalized, and recruitment has begun. Enrollment of participants started in April 2025. By the end of April, 127 participants had completed baseline surveys and HIV/STI self-tests.

## Discussion

### Key Innovation Points

This prospective cohort study will be uniquely designed to evaluate the effectiveness of an internet-based intervention in reducing HIV-related high-risk behaviors and the prevalence of HIV and other STIs among university student MSM. Beyond addressing the primary study objectives, the research will innovatively integrate digital engagement strategies with peer-led support, representing a pioneering approach within this population.

Specifically, the study will establish a dedicated intervention cohort that will utilize social networking platforms to deliver continuous behavioral interventions, promote HIV/STI testing, facilitate service referrals, and provide financial subsidies to support access to PEP.

A key innovation of this study will be the application of the Network Intervention Cohort Peer Model, which will involve recruiting experienced staff from MSM CBOs as trainers and engaging university student MSM volunteers as frontline interventionists. This model is expected to enhance the cultural relevance and acceptability of the intervention while addressing critical limitations of conventional peer education programs.

Furthermore, all interventions will be delivered entirely online, aligning with current trends in MSM-focused health promotion. The intervention package will integrate both behavioral and biomedical components—including the discreet distribution of condoms and lubricants by mail, as well as financial subsidies to support timely initiation of PEP when indicated. Prior research has demonstrated that eliminating financial barriers is a key strategy for empowering MSM to access and sustain engagement with essential HIV prevention services [28].

Recent regulatory tightening surrounding CBO activities—particularly in relation to direct engagement with university students—has significantly constrained the scope of traditional peer education efforts. While Chengdu has previously mobilized college student volunteers through partnerships with local CDCs and AIDS Prevention Associations, such initiatives have generally been broad-based and not specifically tailored to the distinct needs of university student MSM.

Against this backdrop, our project will represent the first known effort in China to design and implement a comprehensive, peer-led network intervention model specifically targeting this demographic.

Despite the study’s innovative strengths, several anticipated operational challenges merit careful consideration.

### Standardization of Volunteer Training and Mentoring

The project relies on CBO staff serving as trainers and student MSM volunteers acting as interventionists. Ensuring consistency and quality in training and mentoring is critical to maintaining intervention fidelity. Variability in training delivery or gaps in knowledge may lead to inconsistent intervention outcomes.

To address this, trainers will be selected from experienced CBO staff across Chengdu with a demonstrated track record in intervention delivery and volunteer mentoring. All volunteers are required to complete the entire capacity-building training and pass a posttraining assessment before participating in interventions. During the intervention process, volunteers can consult their trainers at any time regarding operational issues, such as making referrals or responding to participant inquiries, and can also seek support through the project’s online group chat.

### Recruitment and Retention of a Fixed Cohort

Maintaining participant retention throughout the 12-month follow-up period is crucial to ensuring sufficient statistical power and minimizing attrition bias. While multiple recruitment strategies and financial incentives have been planned, challenges in achieving the targeted sample size may still arise.

To mitigate this risk, contingency plans include expanding recruitment channels, such as peer referrals and targeted social media advertisements, if enrollment falls short. Additionally, each participant will be required to provide both their WeChat contact and mobile phone number upon enrollment. Participants will also be informed that this information, along with their mailing address, will be used solely for study-related purposes, such as the confidential delivery of condoms, lubricants, and other prevention materials, which may help improve retention and engagement.

### Data Collection and Baseline Assessment: Ensuring Reliability of Self-Reported Data

The baseline survey collects sensitive data, including sexual behaviors, substance use, and HIV-related risk factors. Due to social desirability bias or privacy concerns, participants may underreport or misreport behaviors, potentially affecting data accuracy.

To address this, volunteers will emphasize the project’s strict confidentiality protocols when inviting participants to complete the questionnaire. Participants will be clearly informed that no PII is collected in the survey, all data are securely stored in the back-end system, and only the project manager has access to detailed records.

This study has limitations. The before-after self-controlled cohort design does not include a concurrent control group, which limits the ability to make causal inferences. However, a randomized controlled trial was not feasible due to ethical and operational considerations—specifically, the local ethics committee’s recommendation that all eligible university students should have access to the intervention resources. To mitigate this limitation, we will compare changes observed in this study with contemporaneous surveillance data from the Chengdu student MSM population, conduct sensitivity analyses to assess secular trends, and interpret outcomes cautiously in light of these contextual factors. Despite these constraints, the design remains appropriate for evaluating real-world implementation and effectiveness under routine public health conditions. While the assumed reduction in incidence may be optimistic, behavioral indicators such as HIV testing and PEP/PrEP uptake serve as sensitive early markers of intervention impact in this short-term cohort. Given the expected rarity of incident infections over 12 months in student MSM cohorts, we interpret incidence changes cautiously while relying on proximal behavioral outcomes with higher short-term sensitivity.

By proactively addressing these anticipated challenges through standardized training, robust recruitment and retention strategies, and comprehensive privacy protections, this study aims to ensure rigorous implementation while generating valuable insights into the feasibility and effectiveness of internet-based, peer-led HIV prevention interventions among university student MSM.
